#### Intervention

Based on our previous intervention we have developed a comprehensive antibiotic stewardship programme to reduce inappropriate prescribing of antibiotics for ARIs in the general population within rural primary care settings [25]. The intervention targets family physicians and patients in township hospitals, as well as the village doctors associated with township hospitals. The interventional activities are designed to fit within the existing policy requirements around antibiotic prescribing, which are detailed in Table 2. In all our training materials we define appropriate use of antibiotics as: (1) for all URTIs other than bacterial pharyngitis and sinusitis any use of antibiotics is considered inappropriate, and (2) for bacterial pharyngitis, sinusitis, otitis media and bronchitis, amoxicillin or penicillin are the first-line recommended antibiotics and are considered appropriate.

**Table 2 Tab2:** Intervention package and, where relevant, equivalent control-arm processes

Targeted group	Intervention arm	Control arm

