#### Patient safety indicator

We will evaluate whether the intervention appears to increase adverse events; for example, because of antibiotics being withheld for appropriate conditions more frequently due to the intervention, by creating and evaluating an indicator of unintended harms. To do this we will use the EMR to track whether any patients subsequently become hospitalised in any hospital in the Shaoguan Prefecture, including its county- and prefectural-level teaching hospitals, due to respiratory infections or sepsis, within 30 days of their index visit to a participating township hospital during the trial period. This will allow us to calculate a cluster-level hospitalisation rate for trial participants as the number of hospitalisations for respiratory infections or sepsis per 100 outpatient consultations. We will compare both patient safety indicators between treatment arms.

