### Sample size

Our sample size is calculated based on our primary APR outcome. Previous exploratory work suggested the existing township hospital APR level to be around 80%. We assume that the treatment will reduce the intervention arm APR by more than 15 percentage points during the trial period, based on how effective the previous related trial was [25], which is viewed as the minimum clinically important effect in the context of the extremely high existing APR levels. Based on our previous trial [25] we assume that the intra-cluster correlation coefficient will be 0.14 in the intervention arm and 0.09 in the control arm here, and based on our exploratory work we assume that we will be able to collect at least 500 eligible prescriptions per township hospital during the trial period, which we assume as our fixed cluster size. Based on these assumptions we estimated that we will require 17 clusters per arm to detect a 15-percentage-point or greater absolute reduction in the APR with 80% power using a two-sided hypothesis test with an alpha of 0.05 [37]. Because our previous trial data indicated potentially important county-level differences in baseline and during-trial-period APR levels and in the magnitude of the treatment effect, we also plan to stratify our randomisation by county. Therefore, this sample size also accounted for an unequal allocation ratio within strata, and, specifically given the number of clusters available in each county, it accounted for a within-county intervention-to-control allocation ratio of 8:9, which we chose in favour of the control arm for logistical purposes.

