#### Patient safety indicators

We will collect all inpatient charts from the EMR managed under the Prefectural Health Information Centre for any patients who are hospitalised (in any hospital within the Shaoguan Prefecture, including its county and prefectural-level teaching hospitals) within 30 days of their index visit to a trial township hospital for an ARI or for sepsis. The Prefectural Health Information Centre will provide de-identified patient charts for review after identifying patients as having visited a trial township hospital within 30 days of becoming hospitals, using patients’ encrypted insurance numbers. We will then have these inpatient charts reviewed by a group of three to five physicians (blinded to the township hospital of all patients) who will decide if the hospitalisation is due to one of the following reasons: (1) not providing antibiotics during the index visit; (2) other inappropriate usage of antibiotics, such as prescribing the wrong antibiotics; (3) side-effects from antibiotics or other medications and (4) undetermined. Any patients who are determined to have been hospitalised due to either the first or second of these reasons will be included in the calculation of the adverse events’ outcome.

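### The adjudicated safety outcome adds withheld-antibiotic admissions to wrong-antibiotic admissions, so the sum can dilute and, under some assumptions, hide a rise in the first

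*Protocol article*

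**What the plan says.** The Outcomes section of the protocol article, under Patient safety indicator, sets out to see whether the programme increases adverse events. Its example of how that might happen is "because of antibiotics being withheld for appropriate conditions more frequently due to the intervention". It defines a cluster-level rate, the "number of hospitalisations for respiratory infections or sepsis per 100 outpatient consultations", and closes with "We will compare both patient safety indicators between treatment arms".

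The second indicator appears under Data collection and management, Patient safety indicators. Three to five physicians, blinded to township hospital, review the charts of admissions within 30 days of the index visit and give each one of four reasons. The first two are "1) not providing antibiotics during the index visit" and "2) other inappropriate usage of antibiotics, such as prescribing the wrong antibiotics". The others are side-effects of medication, and undetermined. The outcome is then defined: "Any patients who are determined to have been hospitalised due to either the first or second of these reasons will be included". Reasons 3 and 4 are not counted. Nowhere does the article compare reason 1 or reason 2 between arms on its own.

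Two other sections bear on this. The Intervention section and Table 2 describe guidelines meant to lower antibiotic prescribing, together with training and record-system prompts on which antibiotic to choose; the training materials state that for certain diagnoses "amoxicillin or penicillin are the first-line recommended antibiotics and are considered appropriate". The Sample size section takes a current antibiotic prescription rate (APR) of about 80% and plans 17 clusters per arm "to detect a 15-percentage-point or greater absolute reduction in the APR with 80% power".

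**The concern.** The two reasons arise in different visits. Reason 1 can occur only where no antibiotic was given, and the programme is meant to enlarge that group. Reason 2 arises mainly where one was given; the programme is meant to shrink that group and to improve the choice made within it. The expected movements are therefore opposite, and adding the two counts lets one offset the other.

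At stake is how the safety result is read. A flat or lower sum could be taken to mean that withholding antibiotics did no harm, while admissions attributed to withholding had in fact risen. The hospitalisation rate does not settle the matter, because it takes in all respiratory and sepsis admissions whatever the reason.

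**Working it through.** **The plan's own figure.** The article gives no rate, margin or power for either safety indicator. Its only sample-size figure is 17 clusters per arm for the APR, which also supplies the planning rates used below. With p0 = 0.80, p1 = 0.65, m = 500 and intra-cluster correlations of 0.09 (control) and 0.14 (intervention):

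- control variance: 0.80 × 0.20 / 500 × (1 + 499 × 0.09) = 0.01469
- intervention variance: 0.65 × 0.35 / 500 × (1 + 499 × 0.14) = 0.03224
- clusters per arm: (1.960 + 0.842)² × (0.01469 + 0.03224) / 0.15² = 16.4, rounded up to 17

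The figure reproduces. It does not itself bear on the safety outcome.

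**Each reason alone.** Assume a constant reason-1 risk per visit without an antibiotic and a constant reason-2 risk per visit with one. Per 100 visits, those without an antibiotic go from 20 to 35 and those with one from 80 to 65.

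- Reason 1: 35 / 20 = 1.75
- Reason 2: 65 / 80 = 0.8125

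**The sum.** Let R be the control-arm ratio of reason-2 to reason-1 admissions, and q the proportional cut in reason-2 risk from better choice. The article gives neither, so both are assumed.

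Ratio for the sum = [1.75 + 0.8125 × (1 − q) × R] / (1 + R)

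| R | q = 0 | q = 25% | q = 50% |
|---|---|---|---|
| 1 | 1.28 | 1.18 | 1.08 |
| 2 | 1.13 | 0.99 | 0.85 |
| 4 | 1.00 | 0.84 | 0.68 |

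In every cell reason 1 has risen by 1.75. The sum is flat or falls when R ≥ 0.75 / [1 − 0.8125 × (1 − q)]:

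- q = 0: 0.75 / 0.1875 = 4.0
- q = 25%: 0.75 / 0.3906 = 1.92
- q = 50%: 0.75 / 0.5938 = 1.26

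Equal risk per visit for the two reasons may look like a neutral choice, but it means R = 80 / 20 = 4.

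**Relaxing the assumptions (q = 0 unless stated).**

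- Newly untreated visits carry half the reason-1 risk: reason 1 rises by (20 + 7.5) / 20 = 1.375. The sum is (1.375 + 1.625) / 3 = 1.00 at R = 2 and (1.375 + 3.25) / 5 = 0.925 at R = 4.
- Reason-2 risk rises by 25% instead of falling: reason 2 becomes 0.8125 × 1.25 = 1.02, and the sum at R = 4 is (1.75 + 4.0625) / 5 = 1.16. Nothing is hidden.

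**Precision.** Take 17 × 500 = 8,500 consultations per arm, R = 2 and q = 25%, and ignore clustering, which flatters power. For assumed control-arm reason-1 rates of 0.05% to 0.5%, power to see the 1.75-fold rise is at most 15% to 84% on reason 1 alone, against about 3% on the sum. At 0.05% only about four control-arm events are expected (8,500 × 0.0005 = 4.25), so that end is rough.

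**The case against.** A reader might infer four stronger things, and the article supports none of them.

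- *That the pooled outcome is the only safety comparison.* It is not. The hospitalisation rate is also compared between arms, so the safety conclusion does not rest on the sum alone. What stands is that the sum is the only adjudicated comparison and that neither indicator isolates reason 1.
- *That the two reasons do move in opposite directions.* This is what the programme is designed to do, not something shown. Reason 2 could rise if reviewers judged an admission after a narrower choice to be a wrong-antibiotic case; that would also be a plausible ground for counting reason 2 as a possible harm.
- *That the outcome cannot answer the protocol's safety question.* The stated question is adverse events in general, and withholding is given as an example. A sum of two inappropriate-use reasons partly answers a net-harm question, though not fully, since medication side-effects are left out. It does not answer the named example.
- *That masking is the likely result.* Without better choice it needs at least four reason-2 admissions per reason-1 admission in the control arm. At 1:1 the sum still points to harm.

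It can also be said that the unseen analysis plan may tabulate the reasons. It may, and the protocol does not rule that out. But the protocol itself fixes the pooled definition, so the split belongs beside it.

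**Conclusion.** The concern holds in a limited form. The protocol fixes an adjudicated adverse-event outcome whose two parts are expected to move in opposite directions, and it compares neither part alone. At the planning APRs and constant risk per visit, a 1.75-fold rise in withheld-antibiotic admissions would appear in the sum as 1.28 (R = 1), 1.13 (R = 2) or 1.00 (R = 4) without better choice, and as 1.18, 0.99 or 0.84 if better choice cuts reason-2 risk by a quarter. Dilution follows whenever reason 2 rises less than reason 1; complete masking depends on R and q, for which the article gives no data, and on newly untreated visits carrying the same risk as those already untreated. The primary outcome is not affected. This is a cheap improvement to how the safety result is read. The material does not show that the safety evaluation fails, nor that the sum has to be demoted.

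**What to change.** Under Patient safety indicators in Data collection and management, keep the combined outcome and add that admissions for reason 1 and for reason 2 will each be compared between arms, per 100 consultations, with confidence intervals. State that the combined outcome alone will not be used to conclude that withholding antibiotics caused no harm.

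The panel already assigns a reason to every reviewed admission, so no new data or chart review are needed. The cost is statistical: each component has fewer events and a wider interval. The text should therefore also say that a null result on reason 1 is not proof of safety and that the interval must be read for the size of harm it leaves open.

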### Statistical analyses

We will report all results according to the ‘Consolidated Standards of Reporting Trials: Extension for Cluster Trials’ (CONSORT) guidelines [41]. Prior to the end of the trial and before the trial dataset is created we will produce a full statistical analysis plan pre-specifying and detailing all planned analyses. In summary though, in our main results paper we will present appropriate descriptive statistics for all relevant patient, family physician, township hospital and village clinic characteristics, along with appropriate summary statistics and their associated 95% confidence intervals for all outcomes by treatment arm at baseline and during the trial. Then for all outcomes we will produce a main set of estimates of treatment effectiveness using cluster-level methods of analysis suitable for cluster trials. This set of estimates will be used as the primary evidence for determining how effective the treatment appears to be for the primary and all secondary outcomes. There will no interim analyses.

For all outcomes these analyses will follow a two-stage process [42]. For the primary outcome and all secondary proportion-based outcomes we will first fit a multiple logistic regression model to the relevant individual-level binary variable from the prescription data, adjusting for (likely) influential individual- and cluster-level covariates, including the cluster-level value of the outcome during the baseline period (we will fully define all adjustment covariates in the analysis plan). We will then use the model’s residuals to create the cluster-level outcome as covariate-adjusted cluster-specific proportions. We will then estimate the treatment effect based on the covariate-adjusted cluster-specific proportions using a stratified (by county) independent *t* test to compare the cluster-level outcome values in each arm. We will repeat this process for the continuous outcome but using a multiple linear regression model to do the initial covariate adjustment. By estimating covariate-adjusted treatment-effect estimates we will reduce the risk of bias in our results due to imbalances in the cluster-randomisation, and we will increase the precision of the estimates. By ultimately estimating treatment effectiveness using a *t* test, for our cluster-level proportion outcomes we will estimate covariate-adjusted risk differences (i.e. absolute differences in cluster-level outcome proportions), as recommended by CONSORT, and for our cluster-level continuous outcome we will estimate treatment effectiveness as a covariate-adjusted mean difference. We will base our inferences about the effectiveness of the treatment on the outcomes by interpreting the 95% confidence intervals around our outcomes’ treatment-effect estimates along with the associated two-sided *t*-statistic based *p* values. We will adjust all confidence intervals and *p* values for our secondary outcomes for ‘multiple comparisons’ using the Holm method [43, 44].

For our main analyses we will including all clusters originally recruited into the trial as per their original treatment allocations, and all patients who are originally established as being eligible and having received treatment in a trial township hospital during the trial period. We will ensure that all eligible patients who received treatment at a trial township hospital during the trial period are included in our main analyses by dealing with any missing outcome and/or covariate data (used in the two-stage process of adjusting for covariates) using multilevel multiple-imputation methods combined with our cluster-level methods of analysis, if needed [45].

To explore the robustness of our main analysis results we will also do a range of sensitivity analyses. Specifically, we will also produce a set of treatment-effect estimates for all covariate-adjusted cluster-level outcomes but without any multiple imputation of outcome or covariate data (used in the two-stage adjustment process), so that only patient prescriptions that include all outcome and covariate data is included in the analyses (these analyses will also include all clusters, as originally recruited and as per their original treatment allocations, and all patients treated during the trial period with any missing outcome or covariate data imputed). Then we will also produce a final set of treatment-effect estimates for all cluster-level outcomes but without any initial covariate adjustment, but with imputation of any missing outcome data (and again including all clusters, as originally recruited and as per their original treatment allocations, and all patients treated during the trial period with any missing outcome or covariate data imputed). We will adjust the confidence intervals and *p* values from each set of sensitivity analysis results for multiple comparisons as per our main analyses to allow comparison.

Lastly, conditional on obtaining ‘statistically significant’ results for our primary outcome, we will also do a small number of pre-planned subgroup analyses of the primary outcome, which will be fully detailed in the analysis plan. These subgroup analyses will be adjusted for the same range of covariates as the main analyses, and will also include all clusters, as originally recruited and as per their original treatment allocations, and all patients treated during the trial period with any missing outcome or covariate data imputed.

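### Fitting cluster-level covariates in a first-stage model without arm and then t-testing the residuals shrinks the estimated effect toward zero: minor with baseline APR alone, material only if the SAP adds several such covariates

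*Protocol article*

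**What the plan says.** The Statistical analyses section of the protocol article sets one two-stage procedure for all outcomes. For proportions, stage 1 is a multiple logistic regression on individual prescriptions, "adjusting for (likely) influential individual- and cluster-level covariates, including the cluster-level value of the outcome during the baseline period". The next step reads "We will then use the model’s residuals to create the cluster-level outcome as covariate-adjusted cluster-specific proportions". The treatment effect is then estimated "using a stratified (by county) independent *t* test to compare the cluster-level outcome values in each arm". Mean costs follow the same route with a linear model.

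The stated reason for adjusting is that "we will reduce the risk of bias in our results due to imbalances in the cluster-randomisation, and we will increase the precision of the estimates". Inference rests on "interpreting the 95% confidence intervals around our outcomes’ treatment-effect estimates along with the associated two-sided *t*-statistic based *p* values".

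Arm is not listed in the stage-1 model. Its omission is the natural reading, because ordinary residuals from a model containing arm would already have the effect removed. Baseline level is the only cluster-level covariate named. The text uses the plural and defers the list: "we will fully define all adjustment covariates in the analysis plan". The degrees of freedom for stage 2 are not stated. An analysis without covariate adjustment is planned, but only as a sensitivity analysis.

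**The concern.** A covariate with one value per hospital competes directly with arm, which also has one value per hospital. With about 34 hospitals, randomisation leaves some chance correlation between the two. If arm is left out of stage 1, the coefficient of the covariate picks up part of any real treatment effect, and that part is gone from the residuals before stage 2 begins. The error runs toward zero whichever way the imbalance falls. The residual spread also does not reflect that cluster-level coefficients were estimated, so a plain t interval is centred on a shrunken value and tends to be too narrow.

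This is the primary estimate for every outcome. The Sample size section treats 15 points as the minimum clinically important effect, so a true effect at that threshold would on average be reported below it. If the cost per percentage-point reduction in APR uses the same estimate, it would be overstated. If the hospitalisation comparison uses the same method, shrinkage toward zero is not the cautious direction there.

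**Working it through.** **Inputs from the Sample size section.** APR 80% in control and 65% in intervention (a 15-point reduction), ICC 0.09 in control and 0.14 in intervention, 500 prescriptions per hospital, 17 hospitals per arm, 80% power, two-sided alpha 0.05.

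**Reproducing the plan's figure.** Clusters per arm = (1.960 + 0.842)² × Σ p(1−p)[ICC + (1−ICC)/m] / 0.15².
- Control: 0.80 × 0.20 × (0.09 + 0.91/500) = 0.01469
- Intervention: 0.65 × 0.35 × (0.14 + 0.86/500) = 0.03224
- 7.849 × 0.04693 / 0.0225 = 16.37, rounded up to 17, as stated

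**Algebra of the shrinkage.** Take the linear form at cluster level, with centred arm T, covariates X and true effect τ. Regressing Y on X alone and then the residuals on T gives an expected estimate of τ × (1 − R²), where R² is from regressing arm on X. Under randomisation the expected R² is about k/(K−1) for k cluster-level covariates and K clusters. With K = 34:
- k = 1: 1/33 = 3.0%
- k = 3: 3/33 = 9.1%
- k = 5: 5/33 = 15.2%
- k = 8: 8/33 = 24.2%

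If the two pilot hospitals come out of the 17 + 17 listed under Recruitment, K = 32 and the figures barely move (1/31 = 3.2%, 5/31 = 16.1%).

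**Simulation with a logistic stage 1.** The set-up was 34 clusters (17:17, allocated 8:9 in one county and 9:8 in the other), the inputs above, beta-distributed hospital APRs, stage 1 without arm, and a county-stratified t test on 30 df. There were 8,000 runs per row, with a true effect of −15 points. Assumptions not in the article: the latent baseline-to-trial correlation r is 0.5 or 0.8, and k counts baseline APR plus k − 1 non-prognostic covariates.

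| k | Mean, r = 0.5 (shrinkage) | Coverage | Mean, r = 0.8 (shrinkage) | Coverage |
|---|---|---|---|---|
| 1 | −14.50 (3.3%) | 94.1% | −14.48 (3.5%) | 93.5% |
| 3 | −13.51 (9.9%) | 92.7% | −13.55 (9.7%) | 91.4% |
| 5 | −12.57 (16.2%) | 90.0% | −12.50 (16.7%) | 85.6% |
| 8 | −11.23 (25.1%) | 83.2% | −11.12 (25.8%) | 74.1% |

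**Comparator.** A cluster-level regression with arm, county and the same covariates fitted together, with df = clusters minus parameters (3,000 runs), gave means of −14.9 to −15.1 and coverage of 93.9 to 95.0% across k = 1 to 8.

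**No true effect (r = 0.5).** The planned method rejected in 4.4% of runs at k = 1, 4.8% at k = 5 and 5.4% at k = 8.

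**Overall accuracy, RMSE = √(bias² + SE²), in points.**
- k = 1, r = 0.8: planned √(0.49² + 3.51²) = 3.54; joint regression 3.46; unadjusted 5.28
- k = 5, r = 0.5: planned √(2.39² + 4.53²) = 5.12; joint regression 5.15; unadjusted 5.34
- k = 5, r = 0.8: planned √(2.53² + 3.42²) = 4.25; joint regression 3.74; unadjusted 5.26

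A further run with k = 1 and r = 0.6 gave 4.32 for the planned method, 4.36 for the joint regression and 5.23 unadjusted.

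**The case against.** The strongest reply is that the large figures depend on a number the article does not give. It names one cluster-level covariate and leaves the list to the SAP. The other covariates described under data collection are patient-level or prescriber-level; they vary within hospitals and add little to this problem. That stands. The rows for k = 3, 5 and 8 are conditional. They show what would follow from a longer list, not what the plan has chosen.

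Four stronger readings are tempting, and the documents do not support them.

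- A reader might infer that the primary analysis is unsound as it stands. With the one named covariate, shrinkage is about 3%, coverage is near nominal and accuracy is about that of the joint regression.
- A reader might infer a risk of false claims of benefit. The test keeps its size under no effect, and the shrinkage runs against finding a benefit.
- A reader might infer that the stated rationale is false. Adjusting for baseline APR does improve precision, and RMSE at k = 1 is well below the unadjusted value. What the rationale overlooks is a small average attenuation caused by the way the adjustment is done.
- A reader might infer that the plan refuses to charge degrees of freedom for the covariates. It is silent, and that detail commonly sits in the SAP.

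The unadjusted sensitivity analysis is free of this shrinkage and might reveal a gross discrepancy, though it would not correct the primary estimate. What remains is that the order of estimation is fixed in this text, and it attenuates a non-zero effect for any k of 1 or more.

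**Conclusion.** The point holds as a recommended, inexpensive improvement, not as a defect that must be repaired before the trial can proceed. When the true effect is not zero, the procedure as described shrinks the risk difference by about k/(clusters − 1).

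For baseline APR alone this is about half a point in 15, which is minor. It becomes material if the SAP adds several cluster-level covariates: about 1.5 points at k = 3 and about 2.5 points at k = 5, with coverage falling as tabulated.

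The conclusion rests on arm being absent from stage 1, which is the natural reading but is not stated in words. The coverage figures also assume a plain stratified t test on 30 df, the values of k shown, and a baseline correlation of 0.5 to 0.8.

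**What to change.** Use stage 1 for individual-level covariates only. In stage 2, replace the stratified t test with a linear regression of the adjusted cluster proportion (or mean) on arm, county, the baseline cluster value and at most a few other pre-specified cluster-level covariates, with df equal to clusters minus fitted parameters. The result is still an adjusted risk difference or mean difference with a t-based interval and p value.

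Two half-measures are not enough:
- Taking k off the stage-2 df leaves the shrinkage and only partly restores coverage (at k = 5, 93.2% for r = 0.5 and 89.4% for r = 0.8).
- Adding arm to stage 1 and leaving it out of the prediction removes the shrinkage, but with a plain t test coverage stays at about 90% at k = 5. With no true effect, that version rejected in 9.9% of runs at k = 5 (r = 0.5).

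The cost is a few lines of analysis text and code, and one degree of freedom per cluster-level covariate. No new data are needed. It should be settled before the SAP is final.
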